### Statistical analyses

Baseline characteristics of participating patients of the two arms will be presented and compared for any meaningful differences at baseline. Outcomes of interest will be analyzed on an intention-to-treat basis. Multilevel modelling using mixed models, which takes into account patients being nested within clusters, will be able to examine whether changes in the outcomes, which are on interval-scale, vary over time as well as across the two (Aphasia ASK and attention control- SSPIP) programs, after adjusting for the effects of any potential confounders (if any). In addition, attrition patterns across the two arms will be examined to determine randomness of missing data, and if required, multiple imputations will be implemented. All statistical analyses will be performed using Stata statistical software. An alpha level of 0.05 will be accepted as significant. The results of the statistical models will be presented in the form of regression coefficients, their 95 % confidence intervals, and effect sizes. The residuals of the fitted models will be examined to ensure that all required assumptions are met. The statistician completing the data analyses will be blinded to group allocation until analysis is completed.

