### Hypotheses

#### Primary hypothesis

People with aphasia who receive the Aphasia ASK intervention will have significantly better outcomes in mood [15] and quality of life [16] at 12 months post stroke compared to those who receive the attention control intervention (SSPIP).

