## Methods

### Design

This is a multicenter cluster-randomized controlled trial. Clusters, which are represented by Health Service Districts, will be randomized to either the experimental intervention or an attention control intervention, with an equal number of Health Service Districts in each arm. Usual care will continue to the intervention and control arms. The usual care provided will be at the discretion of the hospital site and their treatment protocols. Usual care is typically considered as 1 to 2 sessions of aphasia therapy per week in addition to any required rehabilitation for other stroke-related impairments. Documentation of usual care aphasia therapy will occur. Eligible individuals with aphasia and their family members will be invited to participate upon referral to speech-language pathology services, commencing intervention as early as possible in rehabilitation, but no later than 6 months post stroke. Assessments will occur at baseline and at 12 months post stroke.

The Consolidated Standards of Reporting Trials (CONSORT) 2010 extension statement for cluster-randomized trials [20] has been used to guide the research plan. The Standard Protocol Items: Recommendations for Interventional Trials (SPIRIT) 2013 statement [21] has been used to develop the trial protocol. The Template for Intervention Description and Replication (TIDieR) guide [22] has been used to guide the description of the study interventions.

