### Sample size estimates

Sample size calculations were calculated for both primary outcome measures (ALA and SADQ-21). Power calculations on the ALA have been calculated from an intensive aphasia treatment study [26] and an Australian longitudinal aphasia study [27]. Power calculations on the SADQ have been calculated from the Cost analysis of the Communication and Low Mood (CALM) study [28]. The ALA required a larger sample size compared to the SADQ-21, and therefore, the larger sample size required by the ALA was determined necessary to adequately power the study. To achieve a power of 80 % with a 5 % level of significance in comparing the two arms of the study (Aphasia ASK versus attention control - SSPIP), we need 186 patients (93 per arm) with an effect size of 0.367, computed using ALA data (26, 27). The extent to which power is diminished by clustering was considered in relation to the design effect (DE) = 1 + (m -1)r10, where m = the average size of a cluster and r is the intra-class correlation coefficient. Typically, intraclass correlation coefficients are small (<0.02); thus a conservatively estimated intra-class correlation of 0.02 was used. A cluster size of 20 was chosen based on the feasibility of running the intervention, as well as the availability of patients with aphasia within clusters. Thus DE = 1+ (20-1)*0.02 = 1.38, and the total sample size required was calculated as 186 * 1.38 ≈ 258. To account for an attrition rate of 25 % to the 12-month follow-up period, 344 patients would be needed (172 per arm).

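### Fix the primary contrast as the 12-month score adjusted for its own baseline; read as a change-over-time contrast, the analysis gives away power

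*Protocol article*

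**What the plan says.** The primary hypothesis is that people with aphasia in the Aphasia ASK arm "will have significantly better outcomes in mood" and quality of life at 12 months post stroke, compared with the attention control. The Design section states: "Assessments will occur at baseline and at 12 months post stroke". Each patient therefore contributes two scores per measure.

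The Statistical analyses section describes the outcome analysis in one sentence: "Multilevel modelling using mixed models, which takes into account patients being nested within clusters, will be able to examine whether changes in the outcomes" differ over time and across the two programs, after adjustment for potential confounders, if there are any. It does not say whether the baseline score of the outcome is a covariate or whether baseline means are held equal between arms, and it gives no list of random effects. It adds: "An alpha level of 0.05 will be accepted as significant", with results reported as 95% confidence intervals.

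The Sample size estimates section treats the trial as a two-arm comparison: "we need 186 patients (93 per arm) with an effect size of 0.367, computed using ALA data". It then inflates for clustering and for 25% attrition to reach 344. No baseline-to-outcome correlation enters that calculation.

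**The concern.** The hypothesis and the sample size are about a difference between arms at 12 months, while the analysis sentence is about change. With two time points, the usual reading of that sentence is an arm-by-time interaction, and with baseline means left free this is the same contrast as comparing change scores. Subtracting the baseline score in full brings its noise into the contrast. Regressing on the baseline score uses only as much of it as predicts the outcome.

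What is at stake is precision for both primary outcomes (ALA and SADQ-21). The loss is largest when baseline predicts the 12-month score weakly. That may apply to SADQ-21, because patients who screen positive for depressive symptoms are excluded, which narrows the range of baseline mood. The screening instruments are not SADQ-21 itself and no correlation is reported, so this is a possibility and not a finding.

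**Working it through.** **Inputs from the protocol.** Effect size 0.367; 186 patients (93 per arm) before clustering; cluster size 20; intraclass correlation 0.02; 25% attrition; 80% power; 5% level.

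**Assumptions.** rho is not given, so 0.3, 0.5 and 0.7 are shown. The effect size is taken in units of the 12-month SD, the SD is taken as equal at both times, and the same design effect is applied to every contrast.

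**The plan's own figures.**
- Per arm, n = 2(z_alpha + z_power)^2 / 0.367^2. One-sided 5%: 2(1.645 + 0.842)^2 / 0.1347 gives 92 per arm, or 93 with the t distribution, so 186 is reproduced. Two-sided 5%: 2(1.960 + 0.842)^2 / 0.1347 gives 117 per arm, so 186 is not reproduced.
- Design effect: 1 + 19 x 0.02 = 1.38, and 186 x 1.38 = 256.7 (stated as about 258).
- Attrition: 258 / 0.75 = 344.

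The stated N thus fits a one-sided test. That is a separate matter, but it explains why the two-sided powers below start from 71% and not 80%.

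**Variance of each contrast, relative to the 12-month score alone.**
- 12-month score alone: 1
- Change, or arm-by-time with free baseline means: 2(1 - rho)
- 12-month score adjusted for baseline: 1 - rho^2
- Ratio of change to adjusted: 2(1 - rho) / [(1 - rho)(1 + rho)] = 2/(1 + rho)

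Change is worse than ignoring baseline when 2(1 - rho) exceeds 1, that is, when rho is below 0.5.

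**Power.** Evaluable per arm: 258/2 = 129. Effective per arm: 129/1.38 = 93.5. Standardised signal: 0.367 / sqrt(2/93.5) = 2.509. Two-sided power = Phi(2.509/sqrt(v) - 1.960), where v is the relative variance. The 12-month score alone (v = 1) gives 71%.

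| rho | v, change | v, adjusted | ratio | power, change | power, adjusted |
|---|---|---|---|---|---|
| 0.3 | 1.40 | 0.91 | 1.54 | 56% | 75% |
| 0.5 | 1.00 | 0.75 | 1.33 | 71% | 83% |
| 0.7 | 0.60 | 0.51 | 1.18 | 90% | 94% |

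With a one-sided 5% test the pairs are 68% and 84%, 81% and 90%, 95% and 97%.

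**Sensitivity to the common design effect.** If district effects are perfectly stable over time, they cancel from the change contrast and the advantage of adjustment shrinks. A simulation of that case (18 clusters of 14, ICC 0.02, 4,000 runs, no treatment effect) gave empirical SDs of the estimate, change against adjusted, of 0.139 and 0.122 at rho 0.4, 0.113 and 0.104 at rho 0.6, and 0.079 and 0.075 at rho 0.8. The variance ratios are (0.139/0.122)^2 = 1.30, (0.113/0.104)^2 = 1.18 and (0.079/0.075)^2 = 1.11, against 1.43, 1.25 and 1.11 from 2/(1 + rho). The direction is unchanged.

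**The case against.** **The text permits the better analysis.** With randomised arms, the arm-by-time contrast and the 12-month difference estimate the same effect, so there is no conflict of target. A longitudinal model with a common baseline mean is also a mixed model of outcomes over time, and the baseline score is not excluded from the covariates. This stands. The point is therefore a choice to be fixed among permitted analyses, not the correction of a stated error.

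**The size rests on unstated quantities.** This also stands. The protocol does not say whether 0.367 is in units of the 12-month SD or of the change SD. In change units, the change contrast has 71% power and adjustment multiplies 2.509 by sqrt(2/(1 + rho)), giving 3.112, 2.897 and 2.721, or 88%, 83% and 78% at rho 0.3, 0.5 and 0.7. The gap moves but does not vanish. At high rho it is small in 12-month SD units: 4 points at 0.7 and about 1 point at 0.8.

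**The stronger reading.** Because cluster nesting is the only dependence named, a reader might infer that the planned standard errors are wrong. Two mechanisms exist. With no patient effect, the arm-by-time standard error is too large by 1/sqrt(1 - rho); in simulation at rho 0.6 the model standard error was 0.176 against a true SD of 0.113, with type I error 0.2%. With a patient effect but a cluster intercept constant over time, it can be too small. Assuming ICC 0.02, 15 evaluable per cluster and rho 0.3 to 0.7, type I error is 7.4% to 10.5% if district effects correlate 0.5 over time, and 5.9% to 7.2% if they correlate 0.8. The document supports neither conclusion. It does not say that cluster nesting is the only dependence modelled, and it excludes no random effect. The two mechanisms cannot both apply. The second needs a between-time cluster correlation below 1, which is not given; with stable district effects and a patient effect, simulated type I error was 4.5% to 5.4%. Detail of this kind is commonly left to an analysis plan.

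**Conclusion.** The point holds as a free improvement. The stated analysis is framed as change, the hypothesis is framed at 12 months, and handling of the baseline score is not fixed. If the sentence is carried out as an arm-by-time contrast with free baseline means, the cost in two-sided power at 258 evaluable patients is 75 - 56 = 19 points at rho 0.3, 83 - 71 = 12 points at 0.5 and 94 - 90 = 4 points at 0.7.

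Under equal SDs and a common design effect, the direction holds for every rho below 1. The size depends on rho, on the scale of 0.367 and on how stable district effects are over time, none of which the protocol states. That the plan produces invalid standard errors is not established.

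**What to change.** State the primary analysis for ALA and SADQ-21 as a linear mixed model of the 12-month score on arm, the baseline score of the same measure and the urban/nonurban stratum, with a random intercept for Health Service District. Use the same form for each secondary outcome that is measured at baseline.

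If both time points are kept as outcomes, for example to include patients with a baseline score only, hold the baseline mean common to the two arms, and include patient-level covariance and a cluster-by-time random effect. Leaving out either of these terms can distort the standard error of the arm-by-time contrast.

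The cost is wording in the analysis plan. Baseline assessments are already scheduled, and no visit, measure or patient is added.

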### Randomization

A factor that may affect the outcome of this study is the level of psychological services provided to patients in each cluster. A National Stroke Foundation Rehabilitation Services Report (2012) indicated that lower levels of psychological care might be provided to patients with stroke in nonurban areas in Australia. Hence, clusters will be selected in a way such that they represent either urban (capital city) or nonurban (regional/rural) areas. Considering a cluster size of 20, the required sample size of *N* = 344 (see sample size estimates for details) can be achieved from 18 clusters (nine per arm, with five in urban and four in nonurban clusters). However, 20 clusters will be recruited to account for the potential of cluster attrition during the study. See Table 1 for how the 20 clusters will be stratified. Randomization will occur using a computer-generated random number scheme. Sequential numbers will be assigned to each cluster within each stratum, and only the cluster numbers will be sent to the trial statistician to ensure allocation concealment.

**Table 1 Tab1:** Stratification of clusters

	Experimental intervention	Attention control intervention
Urban clusters (*n* = 10)	five clusters	five clusters
Nonurban clusters (*n* = 10)	five clusters	five clusters

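### The arm comparison rests on 18–20 clusters, and neither the analysis nor the sample size allows for so few; with z-based inference the 12-month test would run at about 5.4–6.2% at the planned ICC

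*Protocol article*

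**What the plan says.** Under Randomization, the article says that the required sample "can be achieved from 18 clusters (nine per arm, with five in urban and four in nonurban clusters"), and that "20 clusters will be recruited to account for the potential of cluster attrition during the study". Clusters are stratified as urban or nonurban, five per arm in each stratum (Table 1).

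Under Statistical analyses, it plans "Multilevel modelling using mixed models, which takes into account patients being nested within clusters", to examine whether changes in the outcomes vary over time and between programs, adjusting for potential confounders. It adds that "All statistical analyses will be performed using Stata statistical software", that "An alpha level of 0.05 will be accepted as significant", and that coefficients will be reported with "their 95 % confidence intervals, and effect sizes". It names no estimator (ML or REML), reference distribution or degrees-of-freedom method.

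Under Sample size estimates, the calculation aims "To achieve a power of 80 % with a 5 % level of significance in comparing the two arms". Its only allowance for clustering is a design effect of 1.38, from a cluster size of 20 and an ICC of 0.02.

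**The concern.** A random effect for cluster puts the right variance component into the standard error. It does not remove the uncertainty in estimating that component from 18 or 20 clusters. Two things can then go wrong. ML divides the between-cluster sum of squares by the number of clusters k instead of k − 2, so the variance is biased down. A normal reference uses 1.96 where the t value is 2.12 (16 df) or 2.10 (18 df). Both make intervals too narrow and p-values too small.

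The design effect does not cover this. It corrects the variance for an ICC treated as known and makes no allowance for the number of clusters. An analysis that handles few clusters properly therefore has a power cost that the sample size did not budget for. The choice of reference distribution could also decide a borderline result on either primary outcome, so it should be fixed before the data are seen.

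**Working it through.** **The plan's own figure.** 186 × 1.38 = 256.7 (stated as about 258); 258 / 0.75 = 344. This reproduces, and no step involves the number of clusters. Patients analysed per cluster: 258 / 20 = 12.9 or 258 / 18 = 14.3.

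**Degrees of freedom.** k − 2 = 16 or 18; with a stratum term, k − 3 = 15 or 17.

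**Analytic check, with the between-cluster variance freely estimated.**
- REML with z: size = 2·P(t(k−2) > 1.96) = 6.8% for k = 18 and 6.6% for k = 20.
- ML with z: the standard error shrinks by √((k−2)/k), so the effective cut-off is 1.96 × √(16/18) = 1.85 or 1.96 × √(18/20) = 1.86. Size = 8.3% or 7.9%.

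These are what z inference approaches when the ICC is large enough that the variance estimate rarely hits zero. At small ICC the estimate is often truncated at zero. The model then uses the pooled variance, which pulls the size back down.

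**Simulation.** No treatment effect, equal cluster sizes, k = 18 or 20, 13 or 15 analysed per cluster, 12-month value only, no stratum term, 400,000 replicates per setting. ICC 0.02 is the article's; the other values are an assumed range. Type I error:

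| ICC | ML, z | REML, z | REML, t(k−2) | Cluster-mean t |
|---|---|---|---|---|
| 0 | 4.5–4.6% | 4.1–4.2% | 2.8–3.0% | 5.0% |
| 0.01 | 5.5–5.6% | 4.9% | 3.4–3.6% | 5.0–5.1% |
| 0.02 | 6.2–6.3% | 5.4–5.5% | 3.8–4.0% | 4.9–5.0% |
| 0.05 | 7.4–7.7% | 6.3–6.4% | 4.6–4.7% | 5.0% |
| 0.10 | 7.8–8.3% | 6.5–6.8% | 4.9–5.0% | 5.0–5.1% |

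**Power, two-sided,** effect 0.367, ICC 0.02, 20 clusters of 13: ML with z 76.7%, REML with z 74.3%, cluster-mean t 71.0%, REML with t(18) 69.5%. The cost of a small-sample method is 74.3 − 71.0 = 3.3 to 74.3 − 69.5 = 4.8 points against REML with z, and 76.7 − 71.0 = 5.7 to 76.7 − 69.5 = 7.2 points against ML with z. The rest of the gap to 80% has other causes, chiefly that 93 per arm reproduces only as a one-sided 5% calculation (two-sided needs 117–118). That is a separate matter.

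**Change-over-time model.** With only cluster and patient intercepts, both intercepts cancel from the time-by-arm contrast, which is then tested as if patients' changes were independent within clusters. If changes have an intracluster correlation of 0.02 (assumed), the true variance is larger by 1 + 12 × 0.02 = 1.24 with 13 per cluster. Size = 2·P(Z > 1.96/√1.24) = 2·P(Z > 1.76) = 7.8%. A degrees-of-freedom correction alone does not repair this, because the cluster component is missing from that contrast.

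**The case against.** A reader might infer that the plan commits to large-sample z tests, so that its 5% tests and 95% intervals are simply wrong. The article does not support that. It names neither ML nor a normal reference, and REML with a small-sample correction is fully compatible with its text. Estimator and degrees-of-freedom method are also details that an article commonly leaves to the full protocol or SAP, which are not shown. So the error rates hold only if z inference is used.

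The size of the effect is also easy to overstate. The article regards 0.02 as a conservative ICC. There REML with z is off by less than half a point, and at 0.01 it is at 4.9%. Figures of 7–8% need ML together with an ICC above the planned one. No ICC is given for any secondary outcome, so inflation there cannot be asserted.

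A reader might also compound the error over the two primary outcomes: 1 − (1 − 0.062)² = 12.0%. Most of that is multiplicity, since two independent exact 5% tests already give 1 − 0.95² = 9.75%, and independence of mood and quality of life is itself assumed. It does not belong to this point.

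What stands against the objection is that the sample size is fully worked in the article, and it treats the design effect as the whole cost of clustering. A later SAP can choose the right test but cannot recover the power that was not budgeted.

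**Conclusion.** The point holds in conditional form. The arm comparison has 9–10 clusters per arm, and neither the analysis section nor the sample size section allows for this. If z inference is used, type I error at 12 months is about 5.4% (REML) to 6.2% (ML) at the planned ICC and roughly 6.5% to 8% at an assumed ICC of 0.10, with no inflation near ICC 0. At the planned ICC this is modest, but it can be avoided at little cost.

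The figures assume equal cluster sizes, no stratum or confounder terms and a 12-month comparison. The change-over-time model in the article was examined only through the simple calculation above. The REML column uses a fixed t(k−2) reference as a stand-in for Kenward-Roger or Satterthwaite, which may differ when the cluster variance is estimated as zero.

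**What to change.** State one primary contrast: the difference between arms at 12 months, for example adjusted for baseline. Estimate it by REML with a cluster random effect and Kenward-Roger or Satterthwaite degrees of freedom. Alternatively, use a t test on cluster-level summaries with k − 2 df (k − 3 with the stratum). Take the reported p-values and 95% intervals from that analysis. If a time-by-arm model is kept, add a cluster-by-time random effect so that the contrast is tested at cluster level. Settle this before any unblinded analysis, and acknowledge the power cost next to the sample size.

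The change needs no extra patients or procedures. Intervals widen slightly, and power falls by about 3–5 points against REML with z or 6–7 against ML with z. Part of that lost power came from testing above 5%. The two options are not identical at ICC 0.02: REML with t is mildly conservative (about 4%), while the cluster-level t test holds 5%.

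### The primary model omits the urban/nonurban randomisation stratum and adjusts only for unnamed confounders, which makes the test conservative if the stratum is prognostic

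*Protocol article*

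**What the plan says.** The Randomization section of the protocol article gives the reason for stratifying: "A factor that may affect the outcome of this study is the level of psychological services provided to patients in each cluster". Because such care may be scarcer outside the cities, clusters are classed as urban or nonurban and randomised within those classes. Table 1 puts five clusters per arm in each stratum, 20 in all.

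The Statistical analyses section describes a mixed model with patients nested in clusters, which examines whether changes in the outcomes vary over time and between programs "after adjusting for the effects of any potential confounders (if any"). It names neither the stratum nor any other covariate. Earlier in the same section, the arms' baseline characteristics are to be presented and "compared for any meaningful differences at baseline". No sentence connects that comparison with the choice of covariates. The analysing statistician stays blind to allocation until the analysis is done.

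**The concern.** A factor was judged important enough to stratify on, so the analysis should account for it. The stated adjustment criterion points the other way. A confounder of the arm comparison must be associated with arm, and Table 1 makes stratum and arm unrelated by design. Read literally, the criterion passes over the one covariate that the design calls for.

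In a balanced layout the effect estimate is the same with or without the stratum. What differs is the standard error: any urban-nonurban gap in outcome is counted as unexplained cluster variation although stratification has removed it from the arm comparison. The interval is then wider than the design earns and the test rejects too seldom under the null.

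The same open phrase leaves the covariate list undecided, so the adjusted estimate depends on a later choice.

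**Working it through.** **The plan's own figure.** The Sample size estimates section states "To achieve a power of 80 % with a 5 % level of significance in comparing the two arms of the study", "we need 186 patients (93 per arm"), "with an effect size of 0.367, computed using ALA data".
- With n per arm = 2(z_α + z_β)²/0.367², a two-sided 5% test needs 117 per arm (234 in total). A one-sided 5% test needs 92, or 93 with the noncentral t. The stated 93 is therefore reproduced only one-sided.
- "Thus DE = 1+ (20-1)*0.02 = 1.38"; 186 × 1.38 = 256.7, which the plan rounds to 258.
- 258/0.75 = 344, as stated.

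At 93 per arm, two-sided power before clustering is about 0.70. This explains why the two-sided powers below start near 0.70 rather than 0.80. That shortfall is not caused by the stratum.

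**Inputs for the stratum check.**
- 20 clusters, five per arm per stratum (Table 1).
- 258/20 = 12.9 completers per cluster.
- Total between-cluster variance 0.02 and within-cluster variance 0.98, in SD² units ("a conservatively estimated intra-class correlation of 0.02 was used").
- Two-sided 5% test, effect 0.367 SD.
- Urban-nonurban gap δ: **assumed**, because the documents give none.

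**Range of δ.** Two equal strata differing by δ contribute δ²/4 to the between-cluster variance. To stay within 0.02, δ can be at most 2√0.02 = 0.283.

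**Formulas.** Variance of a cluster mean within stratum: s² = (0.02 − δ²/4) + 0.98/12.9. With the stratum left out, the 20 cluster means carry the gap on 18 residual degrees of freedom, so the expected residual variance is s² + (20/18)(δ²/4). The ratio of interval widths (omitted/included) is

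√{[s² + (20/18)(δ²/4)]/s²} × t₁₈/t₁₇, with t₁₈/t₁₇ = 2.101/2.110 = 0.996.

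- δ = 0.141: s² = 0.0910; √(0.0965/0.0910) × 0.996 = 1.026
- δ = 0.200: s² = 0.0860; √(0.0971/0.0860) × 0.996 = 1.058
- δ = 0.283: s² = 0.0760; √(0.0982/0.0760) × 0.996 = 1.132

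**Simulation** (cluster-level linear model, 100,000 trials per setting):

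| Gap (SD) | Width ratio | Type I error, omitted | Power, omitted | Power, included |
|---|---|---|---|---|
| 0 | 0.997 | 0.050 | 0.71 | 0.70 |
| 0.14 | 1.03 | 0.044 | 0.71 | 0.73 |
| 0.20 | 1.06 | 0.038 | 0.72 | 0.75 |
| 0.28 | 1.13 | 0.027 | 0.72 | 0.80 |

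With the stratum included, type I error is 0.05 in every row.

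**Sensitivity to cluster size.** With no attrition (344/20 = 17.2 per cluster) and δ = 0.283, s² = 0.98/17.2 = 0.0570, and the ratio is √(0.0792/0.0570) × 0.996 = 1.17.

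**Simplifications.** Equal cluster sizes, no lost clusters, one time point, t-based inference on cluster means.

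**The case against.** **A condensed article may leave the covariate list to an analysis plan that is not shown, and the open phrase could be meant to cover the stratum.** The first part stands: the article does not prove that the stratum was never prespecified, and if an analysis plan names it the sponsor need only confirm this. The second part is weak, because the article does state a criterion and a factor balanced by design does not satisfy it.

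**The planned model concerns change over time.** This stands as a condition. With complete data, a gap of the same size at baseline and at 12 months cancels from a time-by-program contrast. Only a stratum difference in change would then matter.

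**The sample size takes no credit for stratification.** This also stands. Under a total intra-class correlation of 0.02, omission leaves power where it would be without stratification. The loss is a gain not taken, not a fall below planned power.

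Some stronger readings are tempting, but the documents do not support them:
- *Covariates will be picked from observed baseline differences.* The article never links its baseline comparison to the adjustment. The wording permits that practice but does not prescribe it.
- *Such picking inflates false positives.* In a simulation with no true effect (N = 258, five covariates with assumed joint correlation 0.3 or 0.5 with outcome, clustering ignored), adjusting only for covariates imbalanced at p < 0.05 gave type I error of 0.049 and 0.046. Inflation, to 0.096 and 0.136, came only from taking the most favourable of all covariate subsets. Blinding the statistician limits that, although it does not fix the set.
- *The loss could be far larger, for example with gaps of 0.3 or 0.5 SD.* Those gaps alone add 0.3²/4 = 0.0225 and 0.5²/4 = 0.0625 to the between-cluster variance, more than the plan's 0.02.
- *Between-cluster variance dominates precision.* At 12.9 completers it is 0.02/(0.02 + 0.98/12.9) = 0.02/0.0960, or 21% of the variance of a cluster mean.

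**Conclusion.** The point holds as a conditional loss of precision. The model as described leaves out the stratum used in randomisation, and its adjustment criterion neither brings the stratum in nor fixes any other covariate.

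If the stratum predicts the 12-month outcome (or change in it, under a time-by-program contrast), the error is on the conservative side, of the size tabulated above, and reaches its upper end only if the stratum accounts for all the between-cluster variance. This rests on assumed gaps, 12.9 completers per cluster and two-sided testing. If the stratum is not prognostic there is no loss, and including it costs almost nothing (width ratio 0.997). The effect estimate is not biased by the omission, and no inflation of type I error has been shown.

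**What to change.** In the Statistical analyses section, replace the open confounder phrase with a fixed specification:
- Include the urban/nonurban stratum as a fixed effect in the primary model. If baseline is modelled as a repeated outcome, add stratum-by-time.
- Use the baseline score of each outcome once, either as a covariate or as a repeated measure.
- Fix this set before unblinding, and state that the baseline comparison is descriptive and does not select covariates.
- Put any other adjustment, for example for time since stroke or aphasia severity, in a labelled sensitivity analysis. These further covariates are partly a matter of preference; nothing in the article requires them in the primary model.

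If a separate analysis plan already does this, a sentence confirming it is enough. The cost is a change of text and one between-cluster degree of freedom (18 to 17 with 20 clusters). No new data are needed.
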